#### Cohort randomization

A cohort randomization model was used rather than subject randomization to allow all participants in a given GLB™ group to obtain the same intervention. At the time of randomization, 12 cohorts (GLB™ groups) were randomized 1:1 to either the personalized lifestyle intervention (PLI) based on genetics, or the standard lifestyle intervention (SLI) based on population-based guidelines. It was anticipated that 12 groups of approximately 7 participants each would be needed to obtain the desired sample size of 88 participants. Prior to obtaining informed consent from participants, randomly permuted blocks were generated using the original generator on an internet-based randomization program [46]. Since participant recruitment was quicker than anticipated and there was an even 1:1 split of a PLI and a SLI group in the last two randomized groups, only 10 of the randomized groups (5 PLI groups, 5 SLI groups) were used, resulting in a total of *N* = 140 participants in the study (mean number of study participants per group ± SD = 14.0 ± 4.1).

#### Recruitment

Participants were recruited from the GLB™ program at the East Elgin Family Health Team (EEFHT). There were two primary methods of recruitment into this program: [1] adults from Elgin and Middlesex Counties in Ontario, Canada were referred to the GLB™ program by healthcare professionals in the area such as registered dietitians (RDs), physicians, nurses, nurse practitioners, and physical therapists; and [2] adults joined the program through word-of-mouth referrals from members of the community. Participants expressing interest in joining the GLB™ program were invited to the EEFHT for an in-person meeting to learn about the NOW Trial, and to provide written, informed consent if they decided to take part in the study. Therefore, participants are highly reflective of typical patients in the GLB™ program. Recruitment occurred from April 2017 until September 2018. This study is registered with clinicaltrials.gov (NCT03015012) and was approved by the Western University Research Ethics Board (108511).

#### Participants: Screening & Informed Consent

Screening and informed consent were completed in person at the EEFHT during the in-person meeting. Inclusion criteria were as follows: BMI ≥ 25.0 kg/m^2^, ≥18 years of age, English-speaking, willing to undergo genetic testing, having access to a computer with internet at least one day per week, and not seeing another healthcare provider for weight loss advice outside of the study. Pregnancy and lactation were considered exclusion criteria.

#### Run-in

Upon obtaining written, informed consent, participants were scheduled for in-person baseline data collection, within approximately 14 days (mean ± SD = 9.3 ± 5.7) prior to the intervention start date. Participants were not given any lifestyle advice during the run-in period.

#### Baseline data collection

All data are entered into the database using unique study codes for each participant and is securely stored in a locked cabinet, in a locked office. Baseline data consisted of a combination of in-person, online, and telephone data collection methods.

Trained research assistants collected 3-day food records over the phone using the validated multiple-pass method [47]. To reduce participant burden, each participant chose to have either 3 separate phone calls (one for each day of intake), or 1 phone call (for all three days of intake). One weekend day and two weekdays were collected. In rare cases where research assistants were unable to reach participants over the phone, the food records were collected in-person at the EEFHT. The food records were then analyzed using the Canadian Nutrient File within the nutritional analysis software program *ESHA Food Processor* (version 11.1).

Participants also completed a self-administered past-month, semi-quantitative, online food frequency questionnaire, the *Canadian Diet History Questionnaire II (CDHQII)*. This questionnaire is a modified version of the *United States Diet History Questionnaire* adapted for Canadian data [48]. Most participants completed this questionnaire away from the EEFHT, but in cases where participants did not have internet access at home (*n* = 3), the CDHQII was self-administered at the EEFHT.

In-person baseline data collection included: measured height and weight (used to calculate BMI), a BIA assessment to obtain body composition data (using the *Body Stat 1500MDD)*, a past-week physical activity recall (used to calculate metabolic equivalents), a baseline demographic questionnaire, a list of medications, and a TPB questionnaire. To optimize reliability, weight and height measurements were taken on the same *Health O Meter Professional* weigh scale and stadiometer, and body composition was assessed using the same BIA machine. The TPB questionnaire was developed based on Ajzen’s Guide to Constructing a TPB Questionnaire [49]. The results for weight, body fat percentage, body fat (kg), lean weight, and water weight from the BIA were communicated to participants during their in-person baseline data collection visit.

To assess possible short-term changes in components of the TPB (e.g. attitudes towards nutrition, physical activity, genetic testing, etc.), the TPB questionnaire was administered twice during the baseline assessment period: once during the one-on-one, in-person meeting (pre-intervention), and once immediately after the first group-based intervention session was delivered (post-intervention).

#### Blinding and allocation concealment

During informed consent meetings, baseline data collection and the run-in period, participants were blinded to their group assignment. However, participants were not blinded to their group assignment during the administration of the second baseline TPB survey (completed immediately after the first group session in order to assess possible changes short-term in key components of the TPB upon receiving either population-based advice or genetic-based advice). Research assistants collecting and analyzing food intake data were also blinded to the study group of the participants and the statistician will be blinded to the group assignments. Since our outcomes included changes in attitudes related to genetic testing for personalized lifestyle advice, as well as change in nutrition and physical activity habits, it was inappropriate to blind the participants throughout the entire duration of the study. Therefore, participants were informed of their group assignment during the first group intervention meeting, as further outlined in section 4.9, below. One author generated the allocation sequence, enrolled participants, facilitated group and one-on-one interventions, collected data, entered data into the database and scheduled participants, and therefore could not be blinded. Allocation was concealed for the other five co-authors.

#### Staggered cohorts

Staggered cohorts have been used to reduce the impact of confounding by indication and have previously been successful in studies comparing active and passive treatment groups [50]. In the present study, staggered cohorts were pre-planned in order to maximize study efficiency and effectiveness. Seasonality and timing of groups were considered in the planning phase to ensure that there was a similar amount of SLI groups and PLI groups offered during the day and evening. Three SLI groups were offered during the day, and 2 SLI groups were offered in the evenings. Likewise, 3 PLI groups were offered during the day, and 2 PLI groups were offered in the evenings. 1 SLI group began in the spring, 2 in the summer, and 2 in the fall. Similarly, 1 PLI group began in the spring, 2 in the summer, 1 in the fall, and 1 in the winter.

#### Interventions

Given its previously documented success [5, 8, 9], the GLB™ program was chosen as the gold standard comparator for this RCT. Furthermore, given that this study is taking place within routine community/clinical practice, it is highly pragmatic with a mean overall PRECIS-2 score of 4.4 (Table 1) [51].

**Table 1 Tab1:** PRECIS-2 Scoring Tool [51]

PRECIS-2 Domain	Score [Likert scale 1 (very explanatory) - 5 (very pragmatic)]
1. Eligibility: To what extent are the participants in the trial similar to those who would receive this intervention if it was part of usual care?	5
2. Recruitment: How much extra effort is made to recruit participants over and above what would be used in the usual care setting to engage with patients?	5
3. Setting: How different are the settings of the trial from the usual setting?	5
4. Organization: How different are the resources, provider expertise, and the organization of care delivery in the intervention arm of the trial from those available in usual care?	4
5. Flexibility (delivery): How different is the flexibility in how the intervention is delivered and the flexibility anticipated in usual care?	4
6. Flexibility (adherence): How different is the flexibility in how participants are monitored and encouraged to adhere to the intervention from the flexibility anticipated in usual care?	4
7. Follow-up: How different is the intensity of measurement and follow-up of participants in the trial from the typical follow-up in usual care?	3
8. Primary outcome: To what extent is the trial’s primary outcome directly relevant to participants?	5
9. Primary analysis: To what extent are all data included in the analysis of the primary outcome?	TBD
Mean score:	**4.4**

Participants joined the GLB™ group session that best suited their availability, and were blinded to the group intervention assignment at this time. As previously detailed, groups were pre-randomized 1:1 to receive either the standard 12-month GLB™ Program curriculum + a summary report of population-based lifestyle recommendations (SLI/Control Group), or a modified 12-month GLB™ Program + a summary report of DNA-based lifestyle recommendations (PLI Group). All participants underwent a group-based weight management program in addition to four one-on-one sessions (one baseline and three follow-up) with a RD. Group sizes ranged from 7 to 20 participants per group at baseline, with a mean group size of 14 participants. At the three follow-up one-on-one sessions, the RD reviewed the information provided in the summary report (population-based recommendations for the SLI group and DNA-based recommendations for the PLI group; refer to Additional files 2 and 3, respectively, for sample reports). One-on-one sessions lasted approximately 30 min. The same RD who completed the one-on-one sessions was also the lead trained lifestyle coach for the GLB™ Program group sessions. This allowed for optimization of intervention reliability in all group and one-on-one sessions. These sessions were highly standardized as outlined in Additional file 4. No additional healthcare professionals above and beyond standard practice were hired to run the intervention at the EEFHT. Interventions took place between May 2017 and September 2019.

##### SLI group meetings (control group)

The standard GLB™ Program curriculum involves group-based education on a sustainable healthy lifestyle and a moderately-low-fat, calorie-controlled nutrition plan as further detailed elsewhere [52]. Standard GLB™ group sessions were 1 h long. The EEFHT expanded the eligibility criteria for this program and offered it to adults with a BMI ≥25 kg/m^2^. In addition to the standard GLB™ Program, participants were provided with an extra 1.5 h group session (the first session), where they were given an overview of population-based information and recommendations for calories, protein, total fat, saturated fat, total unsaturated fat, monounsaturated fat, polyunsaturated fat, meal/snack timing, and physical activity. This information is further detailed in Additional file 2. Upon completion of the 12-month study, participants in the SLI group were given the results of their lifestyle genomics test if they were interested in receiving it.

##### PLI group meetings (intervention group)

The modified GLB™ Program curriculum is outlined in Additional file 4. The modifications allowed participants in this group to follow their DNA-based recommendations, rather than the standard population-based guidelines. For example, if an individual possessed a genetic variant in the FTO gene whereby a moderately high protein diet can enhance weight loss [21], they were given a target for protein, and were taught how to count daily grams of protein (in addition to calories). In comparison, for the standard GLB™ program, every participant was provided with a target for total fat intake and were taught how to count daily fat grams (in addition to calories). Modified GLB™ group sessions were 1 h long. In addition to the modified GLB™ Program, participants were provided with an extra 1.5 h group session (the first session), where they were given an overview of personalized DNA-based information and recommendations for calories, protein, total fat, saturated fat, total unsaturated fat, monounsaturated fat, polyunsaturated fat, meal/snack timing, and physical activity. This information is further detailed in Additional file 3. It should be noted that the genetic intervention is rated to be high-quality based on a recently developed genetic intervention quality assessment tool [11]. The quality assessment is outlined in Additional file 5.

#### Follow-up data collection

Similar to baseline data collection, follow-up data collection involved a combination of in-person, online and telephone data collection methods. All participants were invited to complete follow-up data collection, regardless of their compliance to their intervention’s lifestyle recommendation. Complete follow-up data included: BMI, 3-day food records, the CDHQII past-month online food frequency questionnaire, BIA, a past-week physical activity recall, a follow-up demographic survey and medication list, and a TPB questionnaire. Further details of these measures are indicated above in section 4.6. The TPB questionnaire was administered once at each follow-up time point during the one-on-one in-person sessions. In addition, at the 12-month follow-up, participants were asked one open-ended question: *How has your life changed since you started participating in this program/study (if at all)?* Follow-up data collection commenced in August 2017 and is ongoing until September 2019.

#### Statistical analysis plan

We plan to use SPSS Version 23.0 to conduct all statistical analyses, and the data will be analyzed on an intention-to-treat basis. Generalized linear mixed-effects models will be used to test between group differences from baseline to each follow-up period for each outcome indicator. If significant mean differences are detected, a Tukey’s post hoc test will be used to compare differences by group. General linear regression models will be used to assess interactions between a given genotype of interest and dietary component of interest on BMI and body composition. General linear regression models will further be used to assess interactions between TPB components, study group, and anthropometric measures of weight and body composition. No interim analyses will be completed.

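### GLB groups were randomised, but no analysis in the plan is said to include the GLB group; if it is left out of the between-arm model, the 5% error rate is not held

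*Protocol article*

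**What the plan says.** The Cohort randomization section of the protocol article is explicit about the unit of allocation: "A cohort randomization model was used rather than subject randomization to allow all participants in a given GLB™ group to obtain the same intervention". Twelve groups were randomised, in the expectation of about 7 participants in each. In the event "only 10 of the randomized groups (5 PLI groups, 5 SLI groups) were used", giving 140 participants ("mean number of study participants per group ± SD = 14.0 ± 4.1").

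The Sample size calculation section asks for 37 participants per arm, raised to 44 per arm for 20% dropout. It mentions neither an ICC nor a design effect.

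For the comparison of arms, the Statistical analysis plan section says: "Generalized linear mixed-effects models will be used to test between group differences from baseline to each follow-up period for each outcome indicator". It does not list the random effects. It then names two sets of general linear regressions. One is for genotype-by-diet interactions. The other involves study group: "General linear regression models will further be used to assess interactions between TPB components, study group, and anthropometric measures of weight and body composition". GLB group is mentioned in none of these sentences.

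**The concern.** When whole groups are allocated, the evidence on the arm effect comes from differences between groups, and here there are only 10. Members of one GLB group may resemble each other for reasons unrelated to genetic advice. They chose the group by availability, started in the same season, and shared a programme of 23 group sessions over 12 months. A model with a participant effect for repeated visits, but no group effect, counts that shared variation as if it were independent information about the intervention.

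At stake is the primary superiority claim on body fat percentage, and every secondary comparison of arms. One or two GLB groups that did unusually well or badly could produce a nominally significant result. With 5 groups per arm there is a second difficulty: even with a group effect in the model, a large-sample reference distribution is too liberal, because the between-group variance is estimated from few groups.

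**Working it through.** **Inputs.** From the article: difference 4 points, SD 6.1, power 80%, alpha 5%, dropout 20% (Sample size calculation); 5 groups per arm, mean size 14.0, SD of size 4.1, N = 140 (Cohort randomization). Assumed: ICC from 0.01 to 0.10, because the article gives none; two-sided testing, because sidedness is not stated; one follow-up value per participant.

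**Step 1. Reproduce the plan's figure.** For two independent means,

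n per arm = 2 × [6.1 × (1.960 + 0.842) / 4]² = 36.5, rounded up to 37; total 74.

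This matches the article exactly. A one-sided test would give 29 per arm and does not match. The calculation therefore treats participants as independent.

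**Step 2. Design effect with unequal group sizes.** CV = 4.1 / 14.0 = 0.293, and

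DE = 1 + [(1 + CV²) × m − 1] × ICC.

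With 20% loss, m = 0.8 × 14.0 = 11.2 (same CV), so DE = 1 + 11.16 × ICC. With all 140, m = 14.0, so DE = 1 + 14.20 × ICC.

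**Step 3. Error of an arm test with no group term.** The correct standard error is √DE times the one reported, so

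true two-sided error = 2 × [1 − Φ(1.96 / √DE)].

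| Assumed ICC | DE, 20% loss | √DE | Error, 20% loss | DE, all 140 | √DE | Error, all 140 |
|---|---|---|---|---|---|---|
| 0.01 | 1.11 | 1.05 | 6.3% | 1.14 | 1.07 | 6.7% |
| 0.02 | 1.22 | 1.11 | 7.6% | 1.28 | 1.13 | 8.4% |
| 0.05 | 1.56 | 1.25 | 11.6% | 1.71 | 1.31 | 13.4% |
| 0.10 | 2.12 | 1.45 | 17.8% | 2.42 | 1.56 | 20.8% |

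Example, ICC 0.05 with loss: DE = 1 + 11.16 × 0.05 = 1.56; 1.96 / 1.25 = 1.57; error 11.6%.

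**Step 4. Check by simulation under no effect.** A participant-level t test with 5 against 5 groups of 7 to 20 and 20% loss (6,000 trials per ICC) rejected in 7.7%, 12.2% and 17.3% at ICC 0.02, 0.05 and 0.10. A repeat gave about 7%, 11% and 18%. With all 140 participants (20,000 trials per ICC), it rejected in 5.0% at ICC 0, and in 6.6%, 8.4%, 13.3% and 20.8% at ICC 0.01, 0.02, 0.05 and 0.10. A t test on the group means (8 df) stayed between about 4.4% and 5.4% across all runs.

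**Step 5. Power once the group is respected.** SE = 6.1 × √(2 × DE / n per arm), tested against t on 8 df (critical value 2.306), for a true difference of 4 points:

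| Assumed ICC | Power, 70 per arm | Power, 56 per arm (20% loss) |
|---|---|---|
| 0.01 | 89% | 82% |
| 0.02 | 85% | 78% |
| 0.05 | 74% | 68% |
| 0.10 | 59% | 55% |

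**The case against.** The strongest reply is that the article does not say what a reader might infer, namely that the primary analysis treats participants as independent. It names a mixed-effects model, which is the class of model that can carry a GLB-group effect, and it lists no random terms of either kind. Random-effects structure and the method for degrees of freedom are commonly left to an analysis plan, and one may exist. That stands: the inflation is conditional on the group being omitted and on a positive ICC. The sample size shows how the trial was sized, not how its data will be analysed. The error rates in the working describe a participant-level test, so they show what omission would cost, not that omission will occur. At ICC 0.01 the cost is small: 6.3% by formula, 5.7% in one simulation with loss.

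A reader might also carry these figures over to the two sets of regressions. The article does not support that. The genotype-by-diet regression lists no study-group term. In the regression with Theory of Planned Behaviour (TPB) components, the stated aim is interactions, and an intercept shared within a GLB group largely cancels from an interaction with a person-level score. A simulation without any group term rejected in 4.8% to 5.6% over ICC 0 to 0.10, assuming random intercepts only and a moderator that is not itself clustered.

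What the reply does not remove is that the article chooses group randomisation, sizes the trial for independent individuals, and then has an analysis section in which the randomised unit does not appear.

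**Conclusion.** The point holds in conditional form. The article randomises GLB groups, but its analysis section does not include the GLB group, and its 74 is the figure for independent individuals. If the between-arm model carries only participant-level effects, the true error at nominal 5%, with 20% loss, is about 7% to 8% at ICC 0.02, 11% to 12% at 0.05 and 17% to 18% at 0.10, and somewhat higher with all 140 participants. The size rests wholly on the assumed ICC. The ICC for change in body fat may be lower than for baseline values, and at ICC 0 there is no inflation. The result covers comparisons of arms, not the interaction terms or the genotype-by-diet regression. It is worth settling before analysis because the primary superiority claim depends on it and the correction is cheap.

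**What to change.** In the Statistical analysis plan section, or in the separate analysis plan:

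- State that every between-arm model includes a random intercept for GLB group as well as one for participant.
- Test the arm effect against a small-sample reference distribution based on the number of groups: 10 groups less 2 arms gives 8 df. Do not rely on Satterthwaite degrees of freedom alone, since they can rise well above 8 when the group variance is estimated near zero.
- Confirm the primary result with a t test on the 10 baseline-adjusted group means (8 df).
- In the regression that includes study group, add the same GLB-group term for any main effect of study group that is reported.

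The cost is a few sentences and a few lines of code. The downside is wider intervals and the lower power shown in the second table: with 20% loss, below 80% from an ICC of 0.02 upwards.

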**Methods:**

Patients enrolled in the GLB™ Program were invited to participate in this study. GLB™ groups were randomized 1:1 to receive either the standard GLB™ program + population-based lifestyle advice for weight management, or a modified GLB™ program + personalized, genetic-based lifestyle advice for weight management. The purpose of this study is to determine if the provision of genetic-based lifestyle guidelines is superior to the provision of population-based guidelines in a pragmatic clinical setting to promote changes in: body composition, weight, body mass index, dietary and physical activity habits, as well as attitudes, subjective norms, and behavioural control. The 12-month intervention protocol consists of 23 group-based sessions and 4 one-on-one sessions. Data collection time points include baseline in addition to 3, 6, and 12-month follow up. The comprehensive study design is described in the present manuscript, using both the extended CONSORT checklist for reporting pragmatic trials and the SPIRIT checklist as guidance during manuscript development.

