#### Sample size calculation

Seventy-four participants (*n* = 37 per group) are needed in this study to detect a clinically meaningful difference of 4% in body fat percentage, assuming 80% power, an alpha of 5%, and a standard deviation of 6.1% [43]. We aimed to recruit 88 participants (*n* = 44 per group) to account for the potential dropout rate of 20%. While minimal research exists outlining a clinically meaningful change in body fat percentage, a 5% change in weight (which would come from fat mass, water weight and/or muscle mass) is often reported to be clinically meaningful [44]. Furthermore, clinical experience from the registered dietitians involved in this study helped to determine the clinically meaningful 4% difference mentioned above. This difference has also been supported in published reference standards of body fat percentage in Caucasian adults which indicate that a 4% change in body fat percentage is associated with a 1 – 2 decile change on the reference standards charts [45].

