#### Outcomes

The primary outcome in this study is change in percent body fat. Secondary outcome measures include changes in: dietary intake (calories, fat, protein, carbohydrates, unsaturated fat including mono- and poly-unsaturated fat, saturated fat, and sodium), physical activity, attitudes, subjective norms, behavioural control, intention to make lifestyle changes, weight and BMI.

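### No visit is named for the primary outcome, the analysis rule tests it at 3, 6 and 12 months, and the Tukey step as worded does not adjust across visits

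*Protocol article*

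**What the plan says.** The Outcomes section of the protocol article defines the primary outcome without a time point: "The primary outcome in this study is change in percent body fat". The primary objective, under Objectives, gives none either. The Abstract lists the visits: "Data collection time points include baseline in addition to 3, 6, and 12-month follow up".

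Under Statistical analysis plan, generalized linear mixed-effects models are to "test between group differences from baseline to each follow-up period for each outcome indicator". If a significant difference is found, "a Tukey’s post hoc test will be used to compare differences by group". No order of testing, split of alpha or overall test across visits is stated.

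The Sample size calculation sizes the trial to "detect a clinically meaningful difference of 4% in body fat percentage", "assuming 80% power, an alpha of 5%, and a standard deviation of 6.1" percent, and arrives at 74 participants, 37 per group. It attaches no visit to that difference.

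**The concern.** The analysis rule produces three between-arm tests of the one primary outcome, and the article does not say which of them decides the trial. A significant result at 3, 6 or 12 months could each be presented as the primary finding, and choosing the visit after seeing the results would comply with the plan as written. The stated alpha and power describe one test. The only procedure that resembles a multiplicity correction compares arms, not visits, and there are only two arms.

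At stake is the trial's single confirmatory claim: whether superiority on body fat was tested at the 5% level that the sample size assumes.

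**Working it through.** **Inputs from the article.** Difference 4 percentage points, SD 6.1, alpha 5%, power 80%, 37 per group (Sample size calculation); two arms, 1:1 (Interventions); three follow-up visits (Abstract). The article does not give the correlation between the three visit-level test statistics, so it is an assumption and a range is shown. All figures ignore clustering by GLB group.

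**1. Reproduce the plan's own figure.** For one two-sided comparison of means, n per arm = 2 × (1.960 + 0.842)² × 6.1² / 4² = 2 × 7.85 × 37.21 / 16 = 36.5, rounded up to 37, or 74 in total. Power at 37 per arm is 80.5%. A t-based calculation gives 37.5 per arm. A one-sided 5% test gives 58 in total and does not match. The stated size therefore belongs to one two-sided 5% test.

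**2. Does Tukey adjust anything between two arms?** Tukey's critical value on the t scale is the studentized-range quantile for k means divided by √2. For k = 2:

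| df | Tukey | t test |
|---|---|---|
| 72 | 1.9935 | 1.9935 |
| 138 | 1.9773 | 1.9773 |

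The two are the same test. Run by group at each visit, the Tukey step leaves each comparison at 5%.

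**3. Chance of at least one false positive over three visits.** Under independence this is 1 − 0.95³ = 14.3%. For correlated statistics, it was simulated from a trivariate normal distribution with no true effect at any visit, counting draws in which the largest absolute value exceeds 1.96 (2,000,000 draws per case, equal correlations):

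| Assumed correlation | At least one false positive |
|---|---|
| 0.5 | 12.5% |
| 0.7 | 10.9% |
| 0.8 | 9.8% |
| 0.9 | 8.3% |
| 0.95 | 7.3% |

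With serial (AR(1)) correlation of 0.7 to 0.9 between neighbouring visits, the range is 11.4% to 8.7%. Changes measured on the same people from one shared baseline should be positively correlated, so the rows from 0.7 to 0.9 are a more reasonable guide than independence.

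**4. What an overall test would do if one were intended.** Suppose a 3-df test of any group difference had to be significant first. With no effect at any visit, the error is then 4.0%, 3.5%, 3.1% and 2.7% for correlations of 0.5, 0.7, 0.8 and 0.9. If one visit has a true effect large enough to open the gate, the other two are tested unadjusted. The chance of a false positive on at least one of those two is 9.0%, 8.4%, 7.8% and 7.0% for the same correlations.

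**5. Cost of keeping all three visits.** With Bonferroni, each test is at 0.05/3 = 0.0167. Then n per arm = 2 × (2.394 + 0.842)² × 37.21 / 16 = 48.7, rounded up to 49, or 98 in total. Power at 37 per arm falls to 66.5%. One named visit keeps alpha at 5% and the requirement at 74.

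**The case against.** The strongest reply is that the Tukey sentence is conditional: it applies only once a significant difference has been found. That is how one writes an overall model test followed by post hoc comparisons. On that reading the error with no effect anywhere stays below 5% (step 4). If Tukey were run over all six or eight group-by-visit means, it would correct substantially, to about 0.0045 or 0.0025 per comparison. This stands as a possible reading, so a reader who infers that the 5% level is certainly broken goes further than the text allows. But no overall test is stated, the comparison is described as by group, and an overall test does not protect the remaining visits once one has a true effect.

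A second reply is that a condensed article may leave multiplicity detail to a fuller plan, and that a 12-month programme makes 12 months the obvious endpoint. The first part excuses missing detail. It does not excuse a rule that the article itself states and that does not match its own sample size. The second part is reasonable but is nowhere written down.

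Third, 140 participants were enrolled against 74 needed. If they are split evenly, 70 per arm gives 93.1% power even with Bonferroni, before clustering and dropout. Loss of power is therefore not the main worry; the undefined claim is.

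Two further inferences are not supported:

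- A reader might take 14.3% as the error rate. It requires independent tests and is only an upper bound.
- A reader might argue that the 3- and 6-month comparisons are confounded by season, because one PLI group and no SLI group started in winter. Under Staggered cohorts, four of five start seasons match across arms (one spring, two summer and one fall in each), and no size of bias can be derived. It is also not a multiplicity issue.

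The statement that no interim analyses are planned does not answer the point, because the three tests all sit in the final analysis.

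**Conclusion.** The point holds in this form: the primary visit is undefined, the stated rule tests the primary outcome three times, the sample size assumes one test, and control of alpha over visits is not specified and fails on the literal reading. The false-positive chance on the primary outcome is then about 8% to 11%, with 14.3% as the upper bound. It stays above 5% at every correlation tried.

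This rests on two assumptions. Significance at any visit could be claimed as success, which the article permits but does not say. And the correlation between visit-level statistics is 0.7 to 0.9, which the article does not give.

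**What to change.** Name one primary contrast: the between-arm difference in change in percent body fat at 12 months, the end of the intervention. Test it once at two-sided 5% from the mixed model. The model must account for the randomised GLB groups (ten were used, per Cohort randomization); otherwise the nominal 5% is not secured even for a single test. Make 3 and 6 months secondary. Delete the Tukey step, or use Holm over the three visits if all are meant to carry claims.

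State when the visit was chosen. Follow-up data collection began in August 2017, and Blinding and allocation concealment says that one author who could not be blinded collected and entered data. Blinding of the statistician alone therefore does not show that the choice was made without sight of results by arm.

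The cost is a few sentences, with no new data and no change to the 74 required. The downside is that an effect seen only at 3 or 6 months can no longer be claimed as the primary result.
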